## Materials and methods

### Research design

L2L will be evaluated using a two-arm parallel group cluster RCT. Schools will be randomly allocated to a group by an independent researcher via a computer-based random number generator to either an intervention or wait-list control. In Australia, the school year is divided into four terms, each approximately 10 weeks in duration. The study will be conducted across two cohorts (2022 and 2023), with assessments at baseline (between mid-March to June, Terms 1 and 2), intervention end (mid-August to September, Term 3), and follow-up (November to mid-December, Term 4). See Fig 1 for the SPIRIT Schedule Of Enrolment, Interventions, And Assessments. The trial has been prospectively registered with the Australian New Zealand Clinical Trials Registry (registration number: ACTRN12621000376842). The design, conduct and reporting will adhere to CONSORT (Consolidated Standards of Reporting Trials) [27] and TIDieR (Template for Intervention Description and Replication) [28] checklists. The trial has been approved by the University of Newcastle’s ethics committee (reference number: H-2020-0109) and the NSW Department of Education’s State Education Research Applications Process (SERAP; reference number: 2020143).

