**Method:**

L2L will be evaluated using a two-arm parallel group cluster randomised controlled trial. Twenty schools located within a two-hour drive of the University of Newcastle, Australia will be recruited. We will recruit 80 students (40 *peer leaders* and 40 *peers*) from each school (*N* = 1,600). L2L will be implemented in three phases: Phase 1 –*school champions’* training via a professional learning workshop; Phase 2 –*school champions’* delivery of leadership lessons to the *peer leaders*; and Phase 3 –*peer leaders’* delivery of the FMS program to their younger *peers*. The FMS program, consisting of 12 x 30-minute lessons, will be delivered over the course of one school term (10 weeks). Study outcomes will be assessed at baseline (between mid-March to June, Terms 1 and 2), intervention end (mid-August to September, Term 3), and follow-up (November to mid-December, Term 4. This trial was prospectively registered on the Australian New Zealand Clinical Trials Registry (ANZCTR); registration number: ACTRN12621000376842.

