### 2) Lessons taught by school champions to *peer leaders*

The *school champions* will deliver 6 x 40-minute lessons to *peer leaders* in Term 2. The six lessons will include a combination of practical activities and information to support *peer leaders* to deliver the FMS program. The information component will address the four aforementioned dimensions of transformational leadership [30], which have been reframed to support *leaders’* understanding as follows: *i) Role modelling*, *ii) Motivating others*, *iii) Considering others*, and *iv) Helping others to think*. Leaders will also be taught the correct movement skill patterns for six object control skills (i.e., catch, underarm throw, overarm throw, bounce, kick, and straight drive [a cricket skill]). *Peer leaders* will be provided with models of the ideal structure of an FMS session which includes: i) *brief skill introduction*, ii) *fast start activity*, iii) s*kill development* with key teaching points, iv) *skill application* in a small-sided game and v) *reflection*. *Peer leaders* will be trained to provide basic teaching cues, individualised feedback, and opportunities to practice movement skills in a supportive, fun, and encouraging environment.

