### 3) Lessons taught by *peer leaders* to peers

Over the course of a school term (10 weeks), *peer leaders* will deliver 12 x 30-minute FMS sessions to *peers*. *Peer leaders* will form pairs or groups of three, which will then be paired with a group of 4–6 *peers* (i.e., *peer leader*: *peer* ratio of 1:2) by the *school champions* and the *peers’* classroom teachers. To have the opportunity to apply transformational leadership principles, these *peer leaders* will remain with the same *peers* for the entire 10-week duration. The *peer leaders* will be provided with a class set of age-appropriate and purpose-designed “lesson-plans” to use (see [S1 Fig]). While *peer leaders* will be provided with resources and a recommended session structure, they will have guided autonomy in their delivery of sessions. Based on feedback from our initial pilot study [24], *peer leaders* will be provided with some simple behaviour management techniques to assist managing children’s behaviour, but will also be assisted by supervising classroom teachers in situations where required.

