#### Primary outcome (*peer leaders*)

Completed by *school champions* at baseline (Term 1: weeks 8–10 to Term 2), and intervention end (Term 3: weeks 5–10):

*Leadership effectiveness*. *School champions* will be asked to rate *peer leaders’* leadership skills using an adapted version of the Transformational Teaching Questionnaire [40]. The questionnaire was developed to assess the tenets of transformational leadership theory: idealised influence, inspirational motivation, intellectual stimulation, and individual consideration. Using the common stem ‘*The student that I’m rating*…’, the questionnaire includes the following items: ‘behaves as someone that other students can trust’ (idealized influence), ‘is enthusiastic about what other students are capable of achieving’ (inspirational motivation), ‘encourages students to think for themselves’ (intellectual stimulation), and ‘shows that s/he cares about the students s/he is teaching’ (individualised consideration)’. The measure requires respondents to answer four questions for each student, using a five-point scale ranging from ‘0 –*not at all*’ to ‘4 –*frequently’*. The scores of each item are summed to create a composite score. This four-item composite measure of leadership effectiveness was found to have acceptable internal consistency in our pilot (α = 0.89 to 0.92) [24].

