### Statistical analysis

General linear mixed models using the ‘lme4’ package in R software [56] will be used to assess the impact of treatment (L2L or control), time (treated as categorical with levels baseline, intervention end and follow-up) and the group-by-time interaction. The primary endpoint of the study will be intervention end (Term 3: weeks 5–10). Our analyses will be adjusted for the clustering of effects at the class and school levels, using random intercepts. Our mediation analyses will use a full information maximum likelihood procedure in Mplus. To determine whether changes in *peer leaders’* on-task behaviour mediate the effect of the L2L program on teachers’ work-related stress and wellbeing, structural equation models will be used to test the following: (i) the total effect of the program on work-related stress and well-being (C pathways); (ii) the effect of the intervention on the mediators (A pathways); (iii) the mediator effects on teachers’ work-related stress and well-being (B pathways); (iv) the direct effect of the L2L on teachers’ work-related stress and well-being with the inclusion of mediators in the model (Cʹ pathways) and (v) the indirect effect of L2L on teachers’ work-related stress and well-being (AB pathways).

To determine whether changes in *peers’* fundamental movement skills mediate the effect of the L2L program on their executive functioning, structural equation models will be used to test: (i) the total effect of the program on executive functioning (C pathways), (ii) the effect of the program on the mediators (A pathways), (iii) the mediator effects on executive functioning (B pathways), (iv) the direct effect of the program on executive functioning with the inclusion of mediators (C’ pathways), and (v) the indirect effect of the program on executive functioning (AB pathways). As Mplus does not support bootstrapping with clustered data, single-level bootstrap confidence intervals will be compared with confidence intervals adjusted for clustering.

Data regarding schools’ exposure to potential sources of contamination (or co-intervention) will be assessed via items in school, teacher, and Principal surveys following the intervention period. Potential effects on outcomes will be explored via sensitivity analyses.

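### The stated assessment windows allow baseline ratings after the leadership lessons have begun and primary-endpoint ratings before the movement programme has ended, because no order within a school is fixed

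*Protocol article*

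**What the plan says.** The protocol article gives the timing in several places.

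- **Assessments, general.** Research design sets "baseline (between mid-March to June, Terms 1 and 2), intervention end (mid-August to September, Term 3". It describes terms as "each approximately 10 weeks in duration".
- **Primary outcome.** Teachers acting as school champions rate leadership effectiveness at "baseline (Term 1: weeks 8–10 to Term 2), and intervention end (Term 3: weeks 5–10". No later rating is listed for this outcome.
- **Primary endpoint.** Statistical analysis states: "The primary endpoint of the study will be intervention end (Term 3: weeks 5–10".
- **Leadership lessons (Phase 2).** School champions "will deliver 6 x 40-minute lessons to *peer leaders* in Term 2". Table 1 gives the same term.
- **FMS programme (Phase 3).** The abstract says that the 12 lessons of 30 minutes "will be delivered over the course of one school term (10 weeks". The section on lessons taught by peer leaders also gives one term of 10 weeks. The term itself is not named.
- **Controls.** Wait-list schools receive the programme in Term 4.

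The SPIRIT schedule (Fig 1) is not available in the text reviewed.

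**The concern.** Baseline may be taken in the term in which the leadership lessons are taught. Those lessons teach the construct that the primary outcome measures, and the teacher who gives them is also the rater. At the other end, a programme that needs a whole term and comes after the Term 2 lessons would normally occupy Term 3, but the endpoint window opens halfway through that term.

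The primary contrast is the group-by-time interaction, that is, the difference in change from baseline to intervention end. Any effect already present at baseline is subtracted from it, and any effect still to come at the endpoint is not counted. Nothing later can repair this, because the primary outcome has no further listed assessment and controls start the programme in Term 4. The other peer-leader outcomes, and the peers' skill and fitness outcomes, use the same windows.

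**Working it through.** **1. Setting the windows side by side.** Two timetables show what the text allows.

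- *FMS fills Term 3 (weeks 1–10).* This is the natural inference: lessons in Term 2, endpoint in Term 3, controls in Term 4. The endpoint window then opens after about 5/10 × 12 = 6 of 12 sessions, and only a rating at the end of week 10 follows the last one. Separately, a baseline taken during Term 2 may come after some leadership lessons. A baseline at the very end of Term 2 leaves no room for six Term 2 lessons after it.
- *FMS runs from mid-Term 2 to Term 3 week 5.* The endpoint is then clean. A baseline in Term 2 may overlap the lessons or FMS itself, but a baseline in Term 1 weeks 8–10 does not. The FMS block straddles two terms, which sits awkwardly with a programme described as lasting one school term.

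Peers are exposed only through FMS. Under the first timetable their baseline is clean, and under the second their endpoint is clean. Under either one, only one end can be affected for them.

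**2. The plan's own sample-size figure.** For d = 0.4/0.8 = 0.50, 80% power and two-sided 0.05, the t-based calculation gives 64 per arm, so 128 reproduces. The product 128 × 5.68 = 727 also checks. The stated inputs (40 per school, ICC 0.15) give 1 + 39 × 0.15 = 6.85, not 5.68, and 128 × 6.85 = 877. That is a separate matter. It is used here only to set the starting power.

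**3. Illustrative dilution, endpoint only.** Assumptions, none of them in the documents: FMS fills Term 3, delivery is even, the effect is proportional to lesson minutes, and baseline is clean.

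- Minutes: 6 × 40 = 240 leadership and 12 × 30 = 360 FMS, total 600. FMS adds 36 minutes a week.
- Share received by week w: (240 + 36w)/600. Week 5 gives 420/600 = 70%. The average over weeks 5–10 (w = 7.5) gives 510/600 = 85%. Week 10 gives 100%.

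Power, for 20 schools with 36 per school after 10% loss (720 students) and ICC 0.15:

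- Design effect 1 + 35 × 0.15 = 6.25, and effective N = 720/6.25 = 115.2.
- Standard error of d = √(4/115.2) = 0.1863.
- Non-centrality = d/0.1863, referred to t with 18 df.

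| Primary rating | d | Non-centrality | Power |
|---|---|---|---|
| Week 10 in every school | 0.50 | 2.68 | 72% |
| Spread evenly over weeks 5–10 | 0.425 | 2.28 | 58% |
| Week 5 in every school | 0.35 | 1.88 | 43% |

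Using 800 students, 40 per school and a design effect of 6.85 gives the same rounded powers. With the plan's printed factor of 5.68 and 800 students, they are 80.1%, 66.5% and 50.2%.

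**4. Late baseline, same assumptions.** With the endpoint at week 10, a baseline after 3 of 6 lessons leaves (120 + 360)/600 = 80% of the minutes in the contrast (d = 0.40). A baseline after all 6 leaves 360/600 = 60% (d = 0.30).

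**The case against.** The strongest reply is that the windows are trial-wide. They cover 10 schools in each cohort, and no school need occupy the whole of either. A school could be rated in Term 1, have its lessons early in Term 2, run FMS from mid-Term 2 and be assessed from Term 3 week 5. A school running FMS throughout Term 3 could be rated at the end of week 10. This stands. A reader might infer that no timetable fits the windows, and that is not so.

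The labels also carry meaning. The article has a separate mid-intervention time point for peers' physical activity, so the authors plainly do not intend intervention end to be halfway. The figure that would show the order is missing from the text reviewed, and an article may leave visit scheduling to the full protocol. This too has force. However, the article does fix the primary endpoint, by calendar weeks, in three sections, and the weeks it gives include some that precede completion if FMS fills Term 3.

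Three further inferences go too far.

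- *That baseline raters were already trained, and so biased towards no effect.* The workshop date is not stated, and training could make a rater stricter or more lenient.
- *That peers' outcomes suffer at both ends.* Neither timetable above produces that.
- *That power falls to 48%.* This scales the effect by FMS sessions alone (75% on average, d = 0.375). It gives no credit to the leadership lessons, which teach the primary construct directly and would be complete by Term 3.

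**Conclusion.** The overlap between assessment windows and delivery is real as written, and the text contains no rule that prevents it within a school. Late baselines and early endpoints can dilute the primary contrast relative to the effect of the full programme. The documents do not show that they will.

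The size cannot be derived from the documents. The powers of 58% and 43%, against 72% at d = 0.50, rest on FMS in Term 3, even delivery, an effect proportional to lesson minutes and a clean baseline. The lower figure is the extreme in which every school is rated in week 5. The gap between 72% and the planned 80% exists before any dilution and belongs to the sample-size calculation, not to timing.

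The point goes beyond missing detail, because the primary endpoint is defined by weeks that permit an incomplete intervention. It deserves correction, but it does not show that the trial's design has failed.

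**What to change.** Reconcile the abstract's Method paragraph, Research design, the two sections on lessons (to peer leaders and to peers), Primary outcome and Statistical analysis, so that together they state when FMS is delivered. Then tie assessments to each school's own milestones:

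- complete baseline, including the teacher's rating, before that school's first leadership lesson and preferably before its champions attend the workshop;
- take the primary rating after that school's last FMS session and before controls start in Term 4;
- assess the two schools of a matched pair at the same time, so that calendar differences do not enter the contrast;
- record each school's assessment dates and the sessions delivered by then, and use them in a sensitivity analysis. That analysis is supportive only, because sessions delivered arise after randomisation.

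The cost is a protocol amendment and a tighter testing calendar for 10 schools per cohort. The pressure is greatest at the end of Term 3: if FMS does fill a 10-week term, very little time remains between the last session and Term 4. For that reason the passages on delivery and assessment have to be reconciled together.

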**Fig 1 pone.0279661.g001:**
[figure not shown]
SPIRIT schedule of enrolment, interventions, and assessments. At the time of this paper’s submission, we have begun participant recruitment.

### Sample size calculation

To ensure 80% power to detect a conservative effect of *d* = 0.50 for leadership effectiveness (adjusted between-group difference of ∼0.4 units with standard deviation of 0.8), we required 128 *peer leaders* for a non-clustered trial (two-tailed, *p*<0.05). However, as recommended by CONSORT [27], we adjusted our power calculation for the clustering of effects at the school level using a correction factor of [1+ (m − 1) × ICC], where m = participants per school and ICC = intraclass correlation coefficient. Assuming an average class size of 20 participating students, two classes per school and an ICC for leadership effectiveness of 0.15, the correction factor is 5.68 [i.e., 1 + (40−1) × 0.15]. The required sample size to achieve 80% power with α levels set at *p* < .05 is 727 (i.e., 128 x 5.68). Operating under the assumption that each school has approximately 60 x Stage 3 students (two classes), with a conservative response rate of 67% and allowing for an expected 10% loss to follow-up, we will aim to recruit at least 40 Stage 3 students from each of 20 schools (*N* = 800). We will also recruit 40 Stage 2 students per school (*N* = 800).

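### The stated ICC (0.15) and correction factor (5.68) contradict each other; if 0.15 is the intended ICC, the required sample is 877 rather than 727 and 20 schools give about 77% power, not 80%

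*Protocol article*

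**What the plan says.** All the sample size figures are in the protocol article under *Sample size calculation*. The aim is set out with the words "To ensure 80% power to detect a conservative effect of" d = 0.50 on leadership effectiveness, described as a difference of about 0.4 "units with standard deviation of 0.8". This gives 128 peer leaders "for a non-clustered trial (two-tailed", 5% level).

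That number is then multiplied by 1 + (m − 1) × ICC, with m = 40 (two classes of 20). The text gives "an ICC for leadership effectiveness of 0.15, the correction factor is 5.68", followed by the working in brackets, where 0.15 appears a second time. The clustered requirement for 80% power "is 727 (i.e., 128 x 5.68"). For recruitment, "we will aim to recruit at least 40 Stage 3 students from each of 20 schools", which is 800 peer leaders, with 10% loss to follow-up expected.

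Under *Primary outcome (peer leaders)*, the outcome is four items, each rated 0 to 4, and "The scores of each item are summed to create a composite score".

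**The concern.** The article shows its own calculation and the result does not follow from the inputs. The wrong product is carried into the required number of peer leaders, which is the only justification given for 20 schools on the primary outcome. A reader who repeats the printed formula gets a different sample size and cannot tell which ICC the trial was designed for. If 0.15 is the design value, the 80% power stated for the primary outcome is not what 20 schools of 40 deliver.

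There is also a smaller mismatch of scale. A difference of 0.4 with SD 0.8 fits the mean of four 0–4 items, whereas the defined outcome is their sum, with range 0–16.

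**Working it through.** **Inputs from the article:** two-sided 5% level; d = 0.4/0.8 = 0.50; m = 40; ICC = 0.15; 20 schools; 10% loss. **Assumption:** 10 schools per arm. No ratio is stated, but there are two arms and the schools are pair-matched.

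**1. Unclustered sample.** A two-sample t-test with d = 0.50 and 80% power needs 63.8, so 64, per arm: 128 in total. The protocol's figure reproduces.

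**2. Correction factor.**
- At the stated ICC: 1 + 39 × 0.15 = 1 + 5.85 = 6.85.
- Solving for the ICC that gives 5.68: (5.68 − 1)/39 = 0.12 exactly.
- Solving instead for m at ICC 0.15: (5.68 − 1)/0.15 + 1 = 32.2, which matches no cluster size in the article. At ICC 0.15, m = 20, 36 and 60 give 3.85, 6.25 and 9.85.

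**3. Required number.**
- ICC 0.12: 128 × 5.68 = 727.04, the printed 727.
- ICC 0.15: 128 × 6.85 = 876.8, so 877. This is about 21% more than 727, and above 800 before any loss.

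**4. Power with 20 schools, d = 0.50.** With n = 10m per arm and DE the correction factor, SE(d) = √(2 × DE/n) and power = Φ(0.50/SE − 1.96). For example, at ICC 0.15 and m = 36: DE = 1 + 35 × 0.15 = 6.25, SE = √(2 × 6.25/360) = 0.186, 0.50/0.186 = 2.68, power = 76.5%. The last column uses the same noncentrality with a t distribution on 20 − 2 = 18 degrees of freedom.

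| ICC | Analysed per school | DE | Power (normal) | Power (t, 18 df) |
|---|---|---|---|---|
| 0.15 | 40 | 6.85 | 77.1% | 72.4% |
| 0.15 | 36 | 6.25 | 76.5% | 71.8% |
| 0.12 | 40 | 5.68 | 84.3% | 80.1% |
| 0.12 | 36 | 5.20 | 83.7% | 79.4% |

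A t-test on the effective sample size (N/DE), which matches how 128 was obtained, gives 76.4% and 75.8% in the two ICC 0.15 rows.

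**5. Detectable effect at ICC 0.15.** (1.96 + 0.84) × SE = 2.80 × 0.186 = 0.52 with 36 per school.

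**6. Scale.** With the pilot's internal consistency taken as 0.90 (reported range 0.89 to 0.92) and four items, the mean inter-item correlation is 0.90/(4 − 3 × 0.90) = 0.69. The SD of the sum is then the item SD × √(4 × (1 + 3 × 0.69)) = item SD × 3.5. A summed SD of 0.8 would mean an item SD of 0.8/3.5 = 0.23 on a 0–4 item, which is implausibly small. An SD of 0.8 therefore belongs to the item mean. On the sum, the same d is 4 × 0.4 = 1.6 units with SD 4 × 0.8 = 3.2.

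**The case against.** The strongest reply is that this is a misprint. An ICC of 0.12 reproduces both 5.68 and 727, so the calculation may have been run at 0.12 and 0.15 typed in error. That is a live explanation. A reader might infer from the arithmetic that the trial is underpowered; the article does not support this as an unconditional statement, because the shortfall exists only if 0.15 was the design value. What remains is that 0.15 is printed in both the words and the formula, and nothing elsewhere in the article corrects it.

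Three other stronger readings are tempting and should not be made.

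- **Attrition.** A reader might note that 800 less 10% is 720, below 727, and conclude that loss is not covered even on the printed figure. That keeps the factor at m = 40 after students have been lost. With 36 per school and ICC 0.12 the factor is 5.20 and the requirement is 128 × 5.20 = 666, which 720 covers.
- **Degrees of freedom.** The figures on 18 degrees of freedom come from a stricter method than the protocol's. The design-effect formula is standard, so its use is not an error; those figures are a sensitivity check.
- **The 0.4-unit difference.** A reader might fear that results on the summed score will be judged against 0.4 units. Nothing in the article says so.

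It is also fair to say that the power figures describe a simple comparison of means, whereas *Statistical analysis* plans a mixed model that uses the baseline. If, as an assumption, baseline adjustment removed 10% or 20% of the variance, power at ICC 0.15 with 36 per school would be 81% or 85% (normal). The article gives no baseline correlation, and it calls its target difference adjusted, so some of that gain may already be counted. This is a caveat on the size of the shortfall and does not reconcile 0.15 with 5.68.

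**Conclusion.** The calculation is wrong as written: an ICC of 0.15 with 40 per school gives 6.85, not 5.68. The consequence depends on which figure was intended.

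- **If 0.15:** the required number is 877, 800 is too few, and 20 schools give about 77% power. The shortfall against 80% is 3 to 4 points by the protocol's type of calculation, and about 8 points on 18 school-level degrees of freedom.
- **If 0.12:** 727 and the plan for 20 schools stand with about 84% power (79–80% on 18 degrees of freedom), and the error is an ICC misprinted twice.

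These figures assume equal allocation, equal school sizes, d = 0.50 and no gain in precision beyond what is already in d. The scale mismatch is real but secondary: d is scale-free, so 128 and everything derived from it are unchanged.

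**What to change.** State which ICC was used in the calculation.

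- If it was 0.15, replace 5.68 with 6.85 and 727 with 877, and restate what 20 schools deliver: about 77% power for d = 0.50, or 80% power for d of about 0.52, after the expected loss. The 18-degrees-of-freedom power of about 72% can be added as a sensitivity figure.
- If it was 0.12, correct the ICC in the sentence and in the bracketed formula; 5.68 and 727 then stand.

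As a secondary edit, give the target difference on the scale to be analysed (about 1.6 units, SD 3.2, on the summed 0–16 score), or define the primary outcome as the item mean.

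The cost is a few words in the sample size section and a note on the trial registry, where the article says amendments will be made available. No extra enrolment is needed. If 0.15 was intended, the stated power becomes slightly less favourable.
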